## Abstract

**Background:**

Retrospective studies suggest that maternal exposure to a severe stressor during pregnancy increases the fetus’ risk for a variety of disorders in adulthood. Animal studies testing the fetal programming hypothesis find that maternal glucocorticoids pass through the placenta and alter fetal brain development, particularly the hypothalamic-pituitary-adrenal axis. However, there are no prospective studies of pregnant women exposed to a sudden-onset independent stressor that elucidate the biopsychosocial mechanisms responsible for the wide variety of consequences of prenatal stress seen in human offspring. The aim of the *QF2011 Queensland Flood Study* is to fill this gap, and to test the buffering effects of Midwifery Group Practice, a form of continuity of maternity care.

**Methods/design:**

In January 2011 Queensland, Australia had its worst flooding in 30 years. Simultaneously, researchers in Brisbane were collecting psychosocial data on pregnant women for a randomized control trial (the M@NGO Trial) comparing Midwifery Group Practice to standard care. We invited these and other pregnant women to participate in a prospective, longitudinal study of the effects of prenatal maternal stress from the floods on maternal, perinatal and early childhood outcomes. Data collection included assessment of objective hardship and subjective distress from the floods at recruitment and again 12 months post-flood. Biological samples included maternal bloods at 36 weeks pregnancy, umbilical cord, cord blood, and placental tissues at birth. Questionnaires assessing maternal and child outcomes were sent to women at 6 weeks and 6 months postpartum. The protocol includes assessments at 16 months, 2½ and 4 years. Outcomes include maternal psychopathology, and the child’s cognitive, behavioral, motor and physical development. Additional biological samples include maternal and child DNA, as well as child testosterone, diurnal and reactive cortisol.

**Discussion:**

This prenatal stress study is the first of its kind, and will fill important gaps in the literature. Analyses will determine the extent to which flood exposure influences the maternal biological stress response which may then affect the maternal-placental-fetal axis at the biological, biochemical, and molecular levels, altering fetal development and influencing outcomes in the offspring. The role of Midwifery Group Practice in moderating effects of maternal stress will be tested.

**Electronic supplementary material:**

The online version of this article (doi:10.1186/s12884-015-0539-7) contains supplementary material, which is available to authorized users.

## Background

### Introduction

Retrospective epidemiological studies suggest that maternal exposure to a severe stressor during pregnancy (e.g., death of a close relative [1], foreign invasion [2]) increases the fetus’ risk for suboptimal growth, and for developing a variety of neurodevelopmental disorders later in life, such as autism [3] and schizophrenia [1,2,4]. The subsequent challenge is to uncover the process that is responsible for these effects: how much of the predictive power of prenatal maternal stress (PNMS) is due to the objective severity of the mother’s exposure to the event itself, how much is due to her subjective level of distress, how much to her hormonal response, and how might these aspects of the stress experience interact to alter risk for the unborn child? In addition, to what extent, and in what way, are the putative effects on the infant and child determined by the mother’s genetic profile, the child’s genetic profile, the child’s sex, and the gestational timing of the stressor?

When testing the fetal programming hypothesis prospectively, animal studies randomly assign pregnant animals to stress or non-stress conditions and find that maternal glucocorticoids (GCs) pass the placental barrier and alter fetal development, in particular influencing the function of the hypothalamic-pituitary-adrenal (HPA) axis and immune system [5-12], causing changes in a wide variety of physiological outcomes for the offspring. In animal studies, the type, severity, and timing of the prenatal stress can be varied and controlled. In humans, however, the gold standards of rigorous experimental methodology are difficult to meet because we cannot randomly assign pregnant women to different stress conditions to determine the effects on the fetus. Most human PNMS research has focused on women experiencing stressful life events. However, most of these events do not occur randomly and may be clustered with other confounding socioeconomic, genetic, and personality, or temperament traits. These potentially confounding variables may have an ongoing influence on the infant and child, independent of the stressful event. Therefore, without the rigor of a randomized, controlled research design, the internal validity of a study is called into question, and the relative contributions of the multitude of biopsychosocial mechanisms responsible for the wide variety of consequences seen in human offspring remain obscure. As long as mechanisms remain obscure, avenues for interventions to alter these consequences will also remain obscure.

In their seminal book, The Social Origins of Depression, Brown and Harris [13] described their rigorous method for determining whether life events that occur prior to women’s diagnosis for major depression may have been partly caused by the women’s developing psychopathology, or were clearly independent of the women’s own agency. Their Life Events and Difficulties Schedule has become the gold standard in social psychiatry research for assessing the severity and independence of life events in order to tease apart the putative causal mechanisms behind depression in women.

With respect to pregnant women and prenatal stress, a sudden, independent environmental event offers an opportunity to circumvent the obstacles to random assignment in human research on PNMS. Many forms of disaster distribute harm in quasi-random fashion, affect sizable communities that include large numbers of pregnant women, and have sudden onsets that allow the researcher to determine the moderating effects of the timing of the event in pregnancy.

In human research, it is also important to distinguish between the pregnant woman’s objective degree of exposure to an event and the intensity of her subjective distress in response to it. Although one may assume that two rats of the same strain will not differ appreciably in their level of distress at having their tails pinched, for example, the human stress response is highly individualized. Appraisal theory, which describes the intrapsychic processes that explain why two people experiencing the same event may have completely different emotional reactions to it [14-16], suggests that the objective degree of exposure to a stressor and the subsequent subjective distress are relatively independent of each other.

The goal of the QF2011 Queensland Flood Study is to capitalize on a natural disaster in order to expand current understanding of how a stressful experience during pregnancy impacts on a woman’s unborn child. Although we study elements of the stress experience from a natural disaster, we believe that our findings could be generalized to other forms of hardship experienced by pregnant women; as such, the Queensland floods serve as a general model of stress exposure in pregnancy, unencumbered by confounding variables, such as maternal genetic predisposition or temperament, that may self-select some women into stressful situations. We aim to determine the relative effects of several objective, subjective, cognitive, and hormonal components of the stress experience by tracking these aspects of stress as they cascade onto biological processes in mother, placenta, and fetus, and onto development through early childhood and beyond. In this article, we will summarize the background literature on PNMS, and describe the protocol for QF2011.

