Effects of PNMS from the ice storm have been found in nearly every domain of child development examined. Significant effects of the degree of maternal objective exposure to the disaster (but not maternal subjective distress) have been found on the children’s cognitive development [47-49], obesity [50], insulin secretion [51], brain development [52], and epigenetic signatures [53]. Effects of maternal subjective distress (and to a lesser extent, objective exposure) have been found on fingerprint asymmetry [54], autistic-like traits [55], and diagnoses of asthma [56] throughout childhood. Objective exposure and subjective distress from the ice storm have been found to interact such that the worst child outcomes are associated with mothers who presented a mismatch between objective exposure and subjective distress, that is, children of mothers with high objective stress but low subjective distress, or with low objective stress along with high distress [55]. There have also been significant timing effects: early pregnancy exposure seems to represent a window of vulnerability for cognition at age 2 years [47], and autism-like traits at age 6½ years [57], while second trimester exposure was associated with shorter gestation lengths and other birth outcomes [58], while worse motor outcomes have been associated with exposure in late pregnancy [59]. The sex of the child has often been found to moderate effects of PNMS: girls were found to be more vulnerable to effects of PNMS on asthma-related symptoms and diagnoses [56] and motor functioning [59], while boys seem to be more vulnerable for effects on fetal growth [58].

Although the Project Ice Storm sample is relatively small (n < 200), statistical power is enhanced by having a range of exposure levels from mild to severe; by the fact that the degree of exposure to the disaster was independent of family psychosocial attributes; by the acute onset of the event which allows exact dating of the stressor in the pregnancy; and by having detailed information on the women, their exposures, and their distress gathered relatively soon after the disaster. The independent nature of the disaster reduces the need to identify and control for all potential confounders, and allows one to disentangle the effects of the women’s objective exposure to the event from their cognitive appraisal of it, and from their subjective distress and hormonal responses.

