##### Maternal mental health

Next, we will examine genetic and psychosocial mediators and moderators of the associations between flood stress and 12-month post-flood maternal outcomes such as symptoms of anxiety (STAI) and PTSD, as well as positive mental health (MHC-SF). We will test the ability of maternal coping style (Brief COPE) and specific candidate genes to moderate the effects of objective stress exposure on mental health outcomes. For women who had the EPDS administered before the floods, we will also determine the moderating effects of pre-flood depression (as measured by the EPDS) in the association between objective stress exposure and maternal mental health outcomes. Our general approach is to use hierarchical multiple linear regression, adding variables into the equation one block at a time. We first regress maternal mental health on exogenous variables such as maternal genotype and demographics; next, we add objective stress exposure; peritraumatic distress and dissociation; then psychosocial variables needed for the interaction (e.g., coping style); and finally we test one interaction at a time (e.g., objective stress-by-coping). We also test moderation and mediation effects directly using the SPSS PROCESS command; the mediation analyses include bootstrapping.

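### Quasi-random flood exposure protects at most the total effect of objective exposure; the planned split through distress, appraisal and cortisol is not protected from confounding by maternal traits

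*Protocol article*

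**What the plan says.** The Introduction rests the design on how disasters spread exposure: "Many forms of disaster distribute harm in quasi-random fashion". It describes the floods as a stress model "unencumbered by confounding variables, such as maternal genetic predisposition or temperament, that may self-select some women into stressful situations". The next sentence sets the target: "We aim to determine the relative effects of several objective, subjective, cognitive, and hormonal components of the stress experience".

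The section on disaster research and Project Ice Storm gives the general argument: "The independent nature of the disaster reduces the need to identify and control for all potential confounders". It adds that the design lets a woman's objective exposure be separated "from their cognitive appraisal of it, and from their subjective distress and hormonal responses".

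The primary research question asks how far objective exposure, appraisal, distress and cortisol explain variance in outcomes. The seventh research question asks whether exposure or distress accounts for altered HPA function in the child. The opening of the data analysis section sets out a cascade from exposure and appraisal, through peritraumatic response, to PTSD symptoms and cortisol, and on to outcomes. For maternal mental health the plan is blockwise regression, and: "We also test moderation and mediation effects directly using the SPSS PROCESS command; the mediation analyses include bootstrapping". Child outcomes are to be analysed with similar regression models.

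**The concern.** If exposure is as good as random, the association of QFOSS with an outcome estimates its total effect. The same does not follow for distress, appraisal or cortisol, which are the woman's own responses. Dividing the total effect into direct and indirect parts requires that the mediator and the outcome have no unadjusted common cause.

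The article itself makes such a common cause plausible:
- **Traits to mediator.** The Introduction says "the human stress response is highly individualized". The prior-trauma paragraph reports that childhood trauma goes with lower adult diurnal cortisol.
- **Traits to outcome.** Of socioeconomic, genetic, personality and temperament traits, the Introduction says "These potentially confounding variables may have an ongoing influence on the infant and child, independent of the stressful event". It uses this to criticise earlier life-event studies, but it applies equally to the subjective and hormonal predictors here.

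At stake is the attribution itself. A common cause acting in the same direction on distress and outcome creates an apparent path through distress and takes the same amount away from the direct effect of exposure.

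**Working it through.** The article gives no bias or error figure on this point, so there is none to reproduce. The check is a linear mediation model with a random exposure.

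**Inputs from the article.** n = 108 + 122 = 230 women recruited; 175 families with data at 2½ years; about 167 expected at 4 years (209 × 0.80 = 167.2).

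**Inputs that are assumptions.** The exposure-to-mediator path a, and a shared-cause loading l, taken as equal on mediator and outcome. The article gives neither, so a range is shown.

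**Model, standardised.** M = aX + lU + error and Y = c′X + bM + lU + error, with X random, U unmeasured and true b = 0. Leaving U out gives:
- bias in b = l²/(1 − a²)
- bias in the indirect effect = a·l²/(1 − a²)
- bias in the direct effect = −a·l²/(1 − a²)
- bias in the total effect = 0
- mediator-outcome error correlation (with c′ = 0) = l²/√(1 − a²)

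Example with a = 0.4 and l = 0.3: 0.4 × 0.09/0.84 = 0.043 of spurious indirect effect, the same amount with a minus sign in the direct effect, and an error correlation of 0.09/0.917 = 0.098.

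**Simulation.** No true mediation, c′ = 0; mediation is declared when both paths are significant at 5%; n = 230.

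| a | l | spurious indirect effect | error correlation | false mediation |
|---|---|---|---|---|
| 0.4 | 0.1 | 0.005 | 0.011 | about 5% |
| 0.4 | 0.2 | 0.019 | 0.044 | 10% |
| 0.4 | 0.3 | 0.043 | 0.098 | 31% |
| 0.4 | 0.4 | 0.076 | 0.175 | 76% |
| 0.1 | 0.1 | 0.001 | 0.010 | 1–2% |
| 0.1 | 0.2 | 0.004 | 0.040 | 3% |
| 0.1 | 0.3 | 0.009 | 0.090 | 9% |
| 0.1 | 0.4 | 0.016 | 0.161 | 22–23% |

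With no shared cause, the joint test declares mediation in about 5% of runs at a = 0.4 and 1–2% at a = 0.1. At n = 175 with a = 0.4, the rates at loadings 0.2, 0.3 and 0.4 are 9%, 25% and 63%.

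**Check with a real total effect.** Assume a total effect of 0.20 that is entirely direct, n = 167 and a = 0.3. At loadings 0.2, 0.3 and 0.4 the total stays at about 0.20, the direct effect falls to 0.19, 0.17 and 0.15, and false mediation is 8%, 23% and 59%.

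**What imperfect adjustment achieves.** Take the same truth with a = 0.5, loadings 0.4 and n = 167. False mediation is 70% unadjusted, and 48%, 26% and 12% after adjusting for a proxy of U with reliability 0.25, 0.50 and 0.75. It returns to 5% only when U itself is in the model.

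Bootstrapping resamples the same confounded association. It describes sampling error and leaves the bias where it was.

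**The case against.** Several points on the other side stand.

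- A reader might infer that the Introduction claims distress and cortisol are themselves free of confounding. It does not: the clause is about self-selection into stressful situations, and the same section stresses individual differences in response.
- The disentangling statement is made about the earlier ice storm cohort, and it speaks of a reduced need for control, not of no need. The next paragraph lists pre-disaster data, to control for earlier psychopathology, among the requirements for a replication.
- PROCESS is named only under maternal mental health, and its mediators are not listed. The primary question is phrased as variance explained.
- The first-block covariates (genotype, demographics) are given as examples in what the article calls a sampling of approaches. The absence of temperament from that list proves little, and full covariate lists belong in the analysis plan. Genetic confounding is partly addressed.
- A reader might also infer that the split is biased and both halves wrong. That cannot be known: at loadings near 0.1 the distortion is negligible. The Introduction also suggests that exposure and distress are relatively independent, and a small exposure-to-distress path shrinks the problem considerably.

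What remains is the inference itself. QF2011 sets out to replicate and extend the ice storm work, adopts the separation of components as an aim, and describes a causal cascade. Nothing in its stated rationale protects that separation. The partial adjustment does not clearly close the gap. Pre-flood EPDS exists only for women already booked at the hospital, and the analysis section uses it as a moderator. No pre-flood temperament measure is listed, and the trait anxiety scale was given at 2½ years.

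**Conclusion.** The point holds in limited form. The as-if-random argument supports at most the total effect of QFOSS. The division into objective, subjective and hormonal parts is not protected from mediator-outcome confounding, which the article's own premises make plausible. The simulated range runs from no appreciable inflation to 76% false mediation. It rests on a linear model, equal loadings, no covariate adjustment and an assumed exposure-to-distress path, so these rates illustrate the risk and do not predict what QF2011 will find. An error correlation of only about 0.1 to 0.2 is enough to produce the larger rates when the path is 0.4. This is an inexpensive improvement that changes what the study may conclude; it does not undermine the total-effect analyses.

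**What to change.** 1. Confine the as-if-random argument to the total effect of QFOSS. Describe effects of distress, appraisal and cortisol, and any direct/indirect split, as associational unless step 3 supports more.
2. In both the mediator and the outcome equation, adjust for pre-flood EPDS where it exists. Add, as supplementary proxies, the Childhood Trauma Questionnaire and MINI episodes dated before 10 January 2011. State that these two are retrospective reports taken after the flood (at 12 months post-flood and at the 16-month assessment), are incomplete, and do not measure temperament.
3. For each indirect effect, report the mediator-outcome error correlation at which it becomes zero. Do not claim an objective-versus-subjective split that vanishes at a small correlation, for example 0.1 to 0.2. Because step 2 offers only proxies, this step matters most.

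Cost: revised wording, some imputation for missing covariates and a routine sensitivity analysis, with no new data collection. The downside is that some indirect effects will be reported as fragile.

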### The fetal programming hypothesis, DOHaD, and prenatal maternal stress

The fetal programming hypothesis [17-22], is often referred to as the Developmental Origins of Health and Disease (DOHaD). It stipulates that physical features and behaviors in offspring of prenatally stressed mothers result from permanent alterations in the structure and function of the offspring’s organs and systems, most likely through the impact of maternal cortisol on the fetus’ developing HPA axis [6]. Because a linear relationship exists between maternal and fetal cortisol levels, relatively small increases in maternal cortisol resulting from anxiety or stress can double fetal concentrations [23], resulting in significant structural changes such as smaller hippocampal volumes [24-27]. Furthermore, anxiety and/or stress in the mother not only increases her own circulating cortisol, it also reduces the activity of the cortisol barrier enzyme, 11β-hydroxysteroid dehydrogenasetype2 (11-βHSD2), in the placenta (which converts maternal cortisol into inactive cortisone before it passes to the fetus), elevating placental and fetal exposure to cortisol [24]. Increased maternal cortisol results in the dysregulation of HPA axis activity in the offspring [20, 21]. This link is important in that dysregulated HPA axis activity is implicated in psychopathological disorders in both adults and children, especially anxiety and depression [28]. The changes in fetal development induced by the maternal physical and emotional environment are not necessarily detrimental to the well-being of the fetus; indeed, some alterations may be adaptive by better preparing the fetus for the postnatal environment. However, high levels of PNMS exposure might have negative effects that override the fetus’ ability to adapt.

### Effect moderators

The association between PNMS and health outcomes may not be simple and linear, as a number of factors may moderate the effects of PNMS on the woman and her unborn child.

Maternal psychosocial variables may be found to moderate the effects of PNMS. For example, considerable literature debates the “social support buffering hypothesis” [29], the idea that effects of a life event will differ according to the degree of social support. There is also an extensive literature in psychology demonstrating that various styles of coping with a life event, emotion-focused versus problem-focused [30, 31], will impact on the subsequent distress experienced. For example, problem-focused coping tends to increase an individual’s self-efficacy and control, and to reduce anger, anxiety, stress, and physiological arousal [32, 33].

The timing of PNMS appears to be an important moderator of PNMS effects on the fetus. It may be less the *type* of disruption to fetal neural development and more the *timing* in utero that determines risk for negative outcomes [34]. Timing effects are a function of (a) the ontogeny of fetal development, (b) alterations in maternal biological and psychological reactivity to stress during pregnancy, and (c) fetal exposure to stress-related biological processes through placental function (e.g., production of CRH) and/or placental transfer of, for example, cortisol [35].

It is also feasible that both maternal and fetal genetics moderate the effects of PNMS on the HPA axis, especially following events that are novel and uncontrollable [36]. In the current project, we focus on the maternal-placental-fetal (MPF) axis because it serves as a prototypical system with well-defined physiological inter-relationships to specify how we analyze interactions between maternal and fetal genotypes, and the environment.

*In utero* stress exposure may have sex-specific outcomes [8, 37-41] with some studies suggesting greater vulnerability in males, and others in females, depending on the outcome measured. Also, in rodents and humans, the activity and sensitivity of placental 11-βHSD2 to stimuli appears to be sex-linked, with greater vulnerability in males, which may partly explain the sex specificity of some stress-induced phenotypes [42].

Finally, effects of PNMS on offspring may be moderated by the postnatal environment. Just as animal studies show that maternal behaviors can partially reverse adverse behavioral and cognitive outcomes in pups [43], similar findings are beginning to emerge in human studies [44, 45].

